## Methods

### Study design and setting

We will implement the geriatric care model using a stepped-wedge cluster randomised clinical trial design. A stepped wedge design is a type of cluster randomized trial design involving sequential roll-out of an intervention to primary care practices (clusters) over a number of time periods [21]. Primary care practices in the control group offer usual care, whereas practices in the intervention group deliver care according to the geriatric care model. By the end of the study, all practices will have started with the intervention. The trial will run over a 24-month period, and will be conducted among a total of 35 primary care practices in the Netherlands, with practices distributed among the regions Amsterdam (18 practices) and West-Friesland (17 practices). The Amsterdam region is of an urban nature, whilst the West- Friesland area can be characterized as an urbanised rural setting. Following participant inclusion, effect measurements will be administered at baseline and at 6, 12, 18, and 24 months (Figure 1). The study received approval by the medical ethics committee of the VU University medical centre. Participants will enrol only after a signed declaration of informed consent.

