### Randomisation

Per region, primary care practices will be randomised using the computer-based ‘Random Allocation Software’ program. In both regions, primary care practices will be allocated to one of a total of four allocation arms by randomization. The allocation arm number designates the starting moment of the intervention with the geriatric care model at practice level (at 0, 6, 12 and 18 months after baseline). Figure 1 shows the number of primary care practices per region, as well as the starting moment of the geriatric care model on cluster level.

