#### Geriatric care model

The geriatric care model aims to enable productive interactions between activated, informed patients and proactive, prepared health care professionals by combining tailored in-home geriatric assessments with strong management. In both the Amsterdam and West-Friesland region, the geriatric care model is integrated into routine practice by an expert geriatric team consisting of an experienced geriatric nurse and an elderly care physician.

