#### Management by expert geriatric teams

During the intervention the geriatric expert teams will carry out the following three main tasks: (1) (quality) management, (2) expert knowledge transfer and (3) building and maintaining local networks of care organisations (Figure 2).

Management of the quality of care delivery by practice nurses and knowledge transfer will constitute of team meetings, training sessions and multidisciplinary patient reviews. First, team meetings will be held on a regular basis, and if required additional coaching and support will be provided to nurses individually. Additionally, as described in the paragraph below, geriatric team members will organize training sessions conform nurses’ educational needs. The sessions provide a platform for peer supervision and encourage knowledge exchange between nurses. Finally, in the event of a practice nurse reporting a complex patient, a multidisciplinary consultation will be organised by the geriatric team for an interdisciplinary review of the client’s situation. The consultation will be attended by a core group, consisting of the practice nurse, the primary care physician, the pharmacists and the geriatric team members. Depending on the situation demanding the consultation, other health care professionals central to the patient’s treatment (e.g. a physiotherapist) will be invited to join.

Throughout the intervention, the two geriatric teams will set up and maintain regional networks of local organisations. In order to facilitate the coordination between providers of care services for older adults in the region, primary care professionals and representatives of various community-based care organisations will meet on a regular basis, with the aim to subsequently enhance the coordination of care on a patient level.

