#### Strategies for implementation

Implementation of the geriatric care model is predicated upon the idea of the professional self-regulation of expert teams and practice nurses. Before the intervention is carried out its main theoretical and practical content is outlined by the research team, where after the development of work routines and protocols is informed by the professionals’ experiences in the field without research staff interference.

To avoid contamination, nurses working with the geriatric care model will not be employed in primary care practices in the control group that have yet to start delivering the intervention.

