#### Analyses

First, characteristics of the participants at baseline will be described and differences between the 4 allocation arms are tested using chi-square tests and ANOVA or non-parametric tests.

Second, effect analyses will be done based on the “intention-to-treat” principle. For both older adults and their primary caregivers, all outcome measures will be compared between the group receiving the geriatric care model and the group receiving usual care using multilevel regression analysis. Multilevel regression analysis takes into account the non-independent nature of hierarchical data and does not require data for a fixed number of observations for all respondents [38]. In the present study, three levels can be distinguished. Repeated observations are clustered within the patient and the patients are clustered within the primary care practices. Potential confounding (due to baseline differences) and effect-modifying will be accounted for during the analysis. If necessary an adjustment will be made for baseline differences between the groups.

In addition to the investigation of the overall effect of the intervention, the stepped-wedge design allows us to study the effects of the duration of the intervention on outcome measures [39]. Therefore, in additional analysis, the interaction between time and intervention will be added to the analyses.

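### The three-level model lets neither practices nor nurses differ in the intervention effect; if nurses differ and are shared between practices, its standard error is too small

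*Protocol article*

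**What the plan says.** Under Analyses, the protocol article compares outcomes by multilevel regression and sets out the hierarchy: "In the present study, three levels can be distinguished", followed by "Repeated observations are clustered within the patient and the patients are clustered within the primary care practices". Practice is the top level. No nurse, expert-team or region term is named. The sample size section likewise allows for clustering by practice only.

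Delivery is organised differently. Under Geriatric assessments by practice nurses, the nurse carries out the six-monthly assessment, reviews it with the primary care physician, writes the care plan and makes both home visits. Under Strategies for implementation, a safeguard against contamination reads: "nurses working with the geriatric care model will not be employed in primary care practices in the control group that have yet to start". The article gives neither the number of nurses nor the number of practices each covers.

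Each region has its own expert team ("the geriatric care model is integrated into routine practice by an expert geriatric team consisting of an experienced geriatric nurse and an elderly care physician"), so there are two teams. Allocation is stratified by region ("Per region, primary care practices will be randomised"), with 18 practices in one and 17 in the other.

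**The concern.** A practice intercept shifts a practice's outcomes equally in control and intervention rounds. A nurse effect appears only once the practice has started. If a nurse serves several started practices, it also runs across them. A practice intercept captures neither feature.

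The rule on nurse employment keeps intervention nurses out of practices still in the control phase. It places no limit on sharing among practices that have started. If such sharing occurs and nurses differ in what they achieve, there are fewer independent delivery units than the 35 practices. The interval for the primary effect would then be too narrow and the test would reject too often.

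**Working it through.** **1. The plan's own figure.** Inputs from Sample size calculations: SD 7.1 (PCS) and 6.6 (MCS), correlation of repeated measurements 0.66 and 0.5, 4 follow-up measurements, ICC 0.02, cluster size 33, alpha 0.05 (taken as two-sided), power 90%, difference 3 points, attrition 20%.

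n per arm = 2 × (1.960 + 1.282)² × SD² × [1 + 3 × rho] / (4 × 3²), multiplied by 1 + 32 × 0.02 = 1.64 and divided by 0.80.

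- PCS: 87.7 × 1.64 = 143.8; 143.8 / 0.80 = 179.8, rounded up to 180.
- MCS: 63.6 × 1.64 = 104.3; 104.3 / 0.80 = 130.3, rounded up to 131.

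Both match the article, so its planning rests on practice clustering alone.

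**2. Model standard error.** Generalised least squares on practice-by-round means, with 35 practices, five rounds and fixed round effects. Starts are at 0, 6, 12 and 18 months, so an arm first contributes treated data at the next measurement. The split of 9/9/9/8 practices per arm is assumed, because the figure showing it is not available. In units of outcome variance, the practice component is 0.02, the patient component (rho − 0.02)/m and the residual (1 − rho)/m. At m = 33 the model SE is 0.0276 SD, or 0.196 points, for PCS and 0.0332 SD, or 0.219 points, for MCS.

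**3. Add the nurse effect to the data but not to the model.** Added variance = nurse variance × sum over nurses of (sum of the estimator's weights on that nurse's treated cells)². Ratio = √(1 + added variance / model variance). Type I error = 2 × [1 − Φ(1.96 / ratio)].

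The documents give no nurse variance. Assumed: 0.5% to 1% of outcome variance, a nurse SD of √0.005 × 7.1 = 0.50 to √0.01 × 7.1 = 0.71 points on PCS. Nurses are assumed to be shared within an arm.

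| Nurse variance | Practices per nurse | PCS, m = 33 | MCS, m = 33 | PCS, m = 26.4 | MCS, m = 26.4 |
|---|---|---|---|---|---|
| 0.5% | 1 | 1.09 | 1.07 | 1.07 | 1.05 |
| 0.5% | 2 | 1.17 | 1.12 | 1.14 | 1.10 |
| 0.5% | 3 | 1.25 | 1.18 | 1.21 | 1.15 |
| 1% | 1 | 1.18 | 1.13 | 1.14 | 1.10 |
| 1% | 2 | 1.32 | 1.23 | 1.26 | 1.19 |
| 1% | 3 | 1.46 | 1.34 | 1.38 | 1.28 |

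Here 26.4 = 33 × 0.80. Over the shared rows, type I error runs from 7.4% (ratio 1.10) to 18.0% (ratio 1.46).

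**4. How much is due to sharing.** The one-practice rows involve no sharing, so they show ordinary variation in the effect between practices. If a practice-level random intervention effect is fitted, what remains at m = 33 is:

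| Nurse variance | Practices per nurse | PCS | MCS |
|---|---|---|---|
| 0.5% | 2 | 1.07 | 1.05 |
| 0.5% | 3 | 1.15 | 1.11 |
| 1% | 2 | 1.12 | 1.09 |
| 1% | 3 | 1.24 | 1.19 |

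Type I error in this table is about 6% to 11%.

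**5. Cross-check by simulation.** 1,000 runs per scenario, with REML refits, 26.4 patients per practice and region fixed. With no nurse effect, the ratio was 1.00 (PCS) and 0.98 (MCS). With 0.5% to 1% and 2 to 3 practices per nurse, it was 1.12 to 1.39 (PCS) and 1.12 to 1.25 (MCS). At 2% and 3 practices per nurse, it was 1.59 and 1.46. Power for 3 points was near 100% throughout.

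**The case against.** **The premise is inferred.** No section says that nurses serve several practices or gives a nurse variance. The employment rule could equally cover a nurse who transfers or stands in temporarily. A reader might infer that the standard errors are too small as a matter of fact. The documents do not support that: with no nurse effect, the model SE is correct. This objection stands, and the point is therefore conditional.

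**Not all of it is a cross-practice problem.** This also stands. At 1% nurse variance, one nurse per practice already gives 1.18 (PCS) and 1.13 (MCS). The remedy therefore begins at practice level.

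**The expert teams.** A reader might infer that one shared team per region also makes the SE too small. That does not follow. Team coincides with region, the randomisation stratum, and two units cannot support a variance estimate. With the two teams taken as fixed, the SE is not too small on their account. A random team effect would matter only for inference to a wider population of teams.

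**The practical effect is modest.** For PCS at m = 33 and the largest ratio, the 95% half-width grows from 1.96 × 0.196 = 0.38 to 0.38 × 1.463 = 0.56 points, against a target difference of 3. This is correct. The risk is to coverage and to false positives for small effects.

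**It may be analysis-plan detail.** The article does not exclude random intervention effects or robust variance, and it says that effect modification will be accounted for. In part this stands. But the article does commit to a named hierarchy, and that hierarchy contains no term for variation in the effect between delivery units.

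**Conclusion.** The point holds conditionally. The stated three-level structure makes no allowance for an intervention effect that varies by practice or by nurse, and the article leaves nurse sharing among started practices open. If nurses differ and are shared, the true SE is 1.17 to 1.46 times (PCS) or 1.12 to 1.34 times (MCS) the model's with 33 patients per practice. With 26.4 it is 1.14 to 1.38 times or 1.10 to 1.28 times. Type I error is about 7% to 18%.

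These figures rest on an assumed nurse variance of 0.5% to 1%, an assumed 2 to 3 practices per nurse and an assumed split across arms. At m = 33, a factor of 1.09 to 1.18 (PCS) or 1.07 to 1.13 (MCS) arises without any sharing. The sample size and the power for 3 points are not in question. This is an inexpensive improvement to the analysis; it does not show that the planned interval is wrong.

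**What to change.** In the Analyses section:

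- Add a random intervention effect at practice level.
- Record which nurse serves which practice, by patient and round, and report that mapping.
- If nurses are shared, add a nurse random effect that acts only in intervention rounds and is crossed with practice. Alternatively, as a sensitivity analysis, use a small-sample robust variance clustered on groups of practices that share a nurse.
- Include region as a fixed term, since it is the randomisation stratum.

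The cost is somewhat wider intervals and one linkage field. The documents do not confirm that this field is already collected: Table 2 describes the nurses' time registrations as average hours per intervention component, with no mention of nurse identity by patient and round. If nurses prove not to be shared, the practice-level term is sufficient and little is lost.

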#### Sample size calculations

Sample size calculations are based on the expected effects of the intervention on the primary outcome, quality of life, measured by the SF-12. Calculations are done using the equation for a longitudinal design [34] and adjusted for the effect of clustering of primary care practices [35]; SF-12 coefficients used in the calculations are derived from previous studies with a study population similar to ours. The number of follow up measurements is 4; Mean cluster size is based on the expected number of participants per cluster at baseline (N = 33). We assume the following: a standard deviation of 7.1 (PCS and 6.6 (MCS) [36], a correlation coefficient of repeated measurements of 0.66 (PCS) and 0.5 (MCS) [37], an intra-cluster correlation coefficient of 0.02 for both PCS and MCS [36], an alpha of 0.05 and a power of 90%. To detect a clinical difference of 3 points [29] on the SF-12 scale between intervention and control groups and assuming an attrition rate of 20%, the study would require 180 (PCS) and 131 (MCS) eligible patients per arm.

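### The three levels named for the effect model include no practice-by-round component; if only practice and patient intercepts are fitted and practices drift differently between rounds, the standard error will be too small

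*Protocol article*

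**What the plan says.** Under Analyses, the article compares all outcomes between the geriatric care model and usual care "using multilevel regression analysis". It states "In the present study, three levels can be distinguished" and lists them: "Repeated observations are clustered within the patient and the patients are clustered within the primary care practices". It does not say whether the random effects are intercepts only or include slopes, and it names no practice-specific time effect. The one time term mentioned is a fixed one, outside the main comparison: "in additional analysis, the interaction between time and intervention will be added to the analyses".

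Under Randomisation, the four arms start the intervention "at 0, 6, 12 and 18 months after baseline". Under Study design and setting, "effect measurements will be administered at baseline and at 6, 12, 18, and 24 months", in 18 plus 17 = 35 practices. Under Sample size calculations, clustering enters as a single value, "an intra-cluster correlation coefficient of 0.02 for both PCS and MCS", with no allowance for the correlation weakening as measurements lie further apart.

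**The concern.** With random intercepts for practice and patient only, two patients of one practice are taken to be equally correlated whether they are measured in the same round or 24 months apart. In a stepped-wedge trial that assumption carries weight. Exposure changes at practice level between rounds, so much of the information on the effect comes from comparing a practice with itself over time. A practice's departure from its own average in one round is shared by all its patients in that round. It enters that comparison directly, and more patients per practice do not average it out. An intercept-only model has no place for this shared departure. It moves the variance into the patient-level residual and then divides it by the number of patients.

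At stake is the validity of the tests on both primary scores, physical (PCS) and mental (MCS): confidence intervals that are too narrow, and a false-positive rate above the stated 5%.

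**Working it through.** **Step 1: the plan's own figure.** The longitudinal formula with 4 follow-up measurements, alpha 0.05 (two-sided) and 90% power is n = 2(1.960 + 1.282)² × SD² × [1 + 3ρ] / (4 × 3²).
- PCS: 2 × 10.507 × 7.1² × 2.98 / 36 = 87.7
- MCS: 2 × 10.507 × 6.6² × 2.50 / 36 = 63.6

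The design effect is 1 + (33 − 1) × 0.02 = 1.64 and attrition is 20%. PCS: 87.7 × 1.64 / 0.8 = 179.8, so 180. MCS: 63.6 × 1.64 / 0.8 = 130.3, so 131. Both agree with the article and are not in question. The inputs are therefore understood as the authors used them.

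**Step 2: inputs for the effect model.**
- From the article: SD 7.1 (PCS) and 6.6 (MCS); correlation of repeated measurements 0.66 and 0.5; intra-cluster correlation 0.02; 35 practices; five rounds; four starting times; 33 patients per practice, or 33 × 0.8 ≈ 26 after 20% attrition.
- Assumed: practices split 9/9/9/8 over the arms; the baseline round untreated in every arm; a closed cohort with equal practice sizes; a fixed effect for each round; a normal reference distribution; and a correlation r of a practice's effect between rounds (practice autocorrelation) of 1.0, 0.95, 0.9, 0.8 or 0.6.

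**Step 3: variances, PCS at r = 0.8.** The total is 7.1² = 50.41.
- Practice, constant over rounds: 0.02 × 0.8 × 50.41 = 0.807
- Practice-by-round: 0.02 × 0.2 × 50.41 = 0.202
- Patient: 0.66 × 50.41 − 0.807 = 32.46
- Residual: 50.41 − 0.807 − 0.202 − 32.46 = 16.94

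Fitted with intercepts only, the model converges on a residual of 16.94 + 0.20 = 17.14, so the practice-by-round part is treated as independent between patients.

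**Step 4: why it matters, in one line.** The round-to-round variance of a mean over 33 patients is 17.14 / 33 = 0.519 according to the model, but 0.202 + 16.94 / 33 = 0.715 in truth. The ratio of standard deviations is √(0.715 / 0.519) = 1.17.

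**Step 5: full calculation.** With V the covariance of the five round means of a practice and X holding the round effects and the exposure indicator:
- reported variance = (Σ X′V_w⁻¹X)⁻¹, with V_w the intercept-only covariance
- true variance = (Σ X′V_w⁻¹X)⁻¹ (Σ X′V_w⁻¹ V_true V_w⁻¹X) (Σ X′V_w⁻¹X)⁻¹
- actual type I error = 2Φ(−1.96 × SE_reported / SE_true)

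For PCS with 33 patients at r = 0.8, SE_reported is 0.196 and SE_true is 0.229. The ratio is 1.168, and 2Φ(−1.96 / 1.168) = 9.3%.

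Actual type I error at nominal 5%, intra-cluster correlation 0.02:

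| r | PCS, 33 patients | PCS, 26 | MCS, 33 | MCS, 26 |
|---|---|---|---|---|
| 1.0 | 5.0% | 5.0% | 5.0% | 5.0% |
| 0.95 | 6.1% | 5.8% | 5.7% | 5.5% |
| 0.9 | 7.1% | 6.7% | 6.4% | 6.1% |
| 0.8 | 9.3% | 8.4% | 7.9% | 7.2% |
| 0.6 | 13.6% | 11.7% | 10.7% | 9.5% |

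**Step 6: with the practice-by-round effect in the model, r = 0.8.** The standard error goes from a reported 0.196 to 0.228 (PCS, 33 patients), 0.220 to 0.249 (PCS, 26), 0.219 to 0.243 (MCS, 33) and 0.246 to 0.267 (MCS, 26). Even the last of these makes the 3-point target 3 / 0.267 ≈ 11 standard errors, so power stays above 99.9%.

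**The case against.** The strongest reply is that the article lists how the data are nested, not which random effects will be fitted. The nesting is described correctly. A three-level model can carry practice-level time effects or be reported with robust standard errors, and a condensed article may leave such detail to a full protocol or analysis plan that is not at hand. This stands in part: a reader might infer that the plan restricts itself to constant practice and patient effects, and the text does not say so. But the article does fix the number of levels at three, and an analyst who follows it literally would set the practice-by-round variance to zero. Allowing a linear random slope per practice does not repair this when the variation is not a linear trend: for PCS with 33 patients the type I error only falls from 9.3% to 9.2% at r = 0.8, and from 13.6% to 13.3% at r = 0.6.

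A second reply is that nothing in the article shows that practices drift. This stands too. A reader might infer that the primary p-values will be too small; that needs a practice autocorrelation below 1, which the article neither gives nor rules out. Nothing ties interviewers to practices, and the changes in nursing and local networks that it describes belong to the intervention. On the other hand, exact constancy over 24 months is the only value at which the intercept model is right, and the article offers no ground for assuming it.

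Third, the figures include fixed round effects, which the article does not name for the main comparison. They therefore describe a reasonable implementation of the plan, not a model it spells out.

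**Conclusion.** The point holds conditionally. The named structure has no practice-by-round component and so suits a stepped-wedge design poorly. The standard error will be understated if two things are true: the fit uses practice and patient intercepts only, and practices change differently between rounds. Under the assumptions listed, the inflation is slight at an autocorrelation of 0.9 or more (at most 7.1%), and material at 0.8 (7.2–9.3%) and 0.6 (9.5–13.6%). A larger intra-cluster correlation would make it worse and a smaller one milder; 0.02 is used because it is the only value in the article. In absolute terms the understatement is at most about 0.06 points on the SF-12 scale, so it would change the conclusion only for a result near the significance threshold. The sample size is unaffected. The change is worth making before analysis because it protects the stated 5% level at little cost.

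**What to change.** State the primary model as a multilevel regression with fixed measurement-round effects, random intercepts for practice and patient, and a random effect for practice by measurement occasion. Keep the last term even if its estimate is small. Use a small-sample degrees-of-freedom method suited to 35 practices, such as Kenward-Roger or Satterthwaite.

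The cost is one more variance component to estimate. If practices do not drift, the standard error hardly changes. If the autocorrelation is 0.8, the reported standard error for PCS goes from about 0.20–0.22 to 0.23–0.25, which is its honest size. Power for a 3-point difference is essentially unchanged.
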